### Recruitment and consent

We will invite consecutive adult patient participants (18 years and older) with chronic musculoskeletal pain (> 3 months) referred to the KHSC Chronic Pain Clinic until we recruit approximately 40 patient participants. Forty participants were determined sufficient to address our feasibility outcomes using a practicality approach [51] and is within an acceptable rule of thumb range for pilot trials [52]. Potential participants will be triaged by a registered health professional from the Chronic Pain Clinic interprofessional team based on referral information and study inclusion/exclusion criteria. A registered practical nurse (RPN) will ask potential participants for consent to be contacted by a research team member. A research associate will then contact the potential participants to provide full information about the trial and invite them to participate. Consenting participants will then be enrolled in the study prior to completing the baseline assessment and scheduling an appointment with the APP.

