### Evaluation and outcome measures

Participants will be asked to complete an online survey through a secure online data collection platform [Qualtrics, Provo, UT, USA [58]] to obtain baseline measures prior to their visit with the APP. Follow-up assessments will be collected electronically (or in person or by phone if requested by the participant) at 3, 6, 9, and 12 months after the initial assessment. If the participant does not complete the electronic survey, follow-up emails and phone calls will be made.

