#### Duration of survey completion

We will consider mean times for the completion of baseline and follow-up surveys of less than 60 min each to be acceptable. Completion times will be measured using the start and end times of the surveys.

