#### Attrition rate

Retention will be evaluated by rate of attrition. An attrition rate of < 20% at 12-month follow-up is considered indicative of feasibility. Research has suggested that > 20% attrition threatens study validity [60].

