### Analysis

Descriptive statistics for all relevant baseline measures and outcomes will be reported, and decisions will be made regarding study feasibility based on the thresholds described under each feasibility outcome (e.g., < 20% attrition, > 80% of assessment items completed, and > 80% of items performed on the treatment fidelity checklist). Means (standard deviation) or medians (interquartile range) for continuous variables and frequencies (percent) for categorical variables will be presented. Quality indicator calculations are presented in the quality standards operationalization table (Additional file 4) and will be presented accordingly for each quality statement.

Health utilization measures will be presented as counts, and costs will first be calculated as the product of resource utilization and the corresponding unit cost. Summing these costs will provide the total costs and will be further assessed at each follow-up interval. The mean cost for the entire study period, as well as the mean cost for each time interval, will be presented.

We will document challenges in the collection and analysis of all data to inform the plan for the full trial where we intend to perform a complete assessment of adherence to quality standards and cost utility analysis.

The transcribed interviews will be analyzed using an interpretive description approach [61] to generate clinically relevant themes. Thematic analysis [63] will be performed by two investigators who will independently code the transcripts. As described by Braun and Clarke [63], the thematic analysis process will include familiarization with the data, production of initial codes, finding and reviewing potential themes, naming themes, and producing a report of the analysis. Identified themes will be used to describe patterns in patient participant and HCP responses to translate their perspectives into meaningful representations of the experience with the APP model of care as they relate to the acceptability of the APP role; barriers, facilitators, and strategies for refining model implementation; and perceived impact on clinical processes and outcomes.

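### The 60-minute survey-burden criterion uses the mean of start-to-end clock times, so one long interruption could produce a false verdict of unacceptable burden

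*Protocol article*

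**What the plan says.** Under Duration of survey completion the protocol article sets the criterion: "We will consider mean times for the completion of baseline and follow-up surveys of less than 60 min each to be acceptable". The next sentence fixes the measurement: "Completion times will be measured using the start and end times of the surveys". The article gives no rule for idle time, interrupted sessions or extreme values.

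The surveys are done online and remotely: "Participants will be asked to complete an online survey through a secure online data collection platform" (Evaluation and outcome measures). The same section provides for chasing: "If the participant does not complete the electronic survey, follow-up emails and phone calls will be made". Surveys are due at baseline and at 3, 6, 9 and 12 months, and may be done in person or by phone on request.

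The Analysis section presents "Means (standard deviation) or medians (interquartile range) for continuous variables". It also says that feasibility decisions rest on the threshold given under each feasibility outcome.

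**The concern.** End time minus start time equals time spent answering only if the respondent works straight through. A tab left open overnight, or a part-finished survey completed after a reminder, would carry its idle hours into the duration. Interruption is plausible here. Respondents have chronic pain, and the battery covers pain, quality of life, three psychosocial questionnaires, adverse events, itemised healthcare use and productivity loss (Participant health outcomes; Cost-utility analysis).

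The threshold is then applied to the mean, the common summary that a single extreme value moves most. The Analysis section's mention of medians governs how continuous variables are described. It does not change the statistic to which the 60 minutes applies.

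At stake is the accuracy of one pre-set feasibility verdict. The error runs one way, because idle time can only lengthen a duration: a survey of acceptable length may be declared not acceptable. Trimming the extreme value after seeing the data would be a post hoc change to the decision rule, so the rule is better settled beforehand.

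**Working it through.** The 60-minute limit is stated without derivation, so there is no figure of the plan's own to reproduce. The check asks how long one interrupted survey must run before the mean is no longer below 60.

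**Inputs from the article**
- Threshold: mean below 60 min (Duration of survey completion).
- Baseline n = 40: recruitment continues "until we recruit approximately 40 patient participants" (Recruitment and consent).
- 12-month n = 33: "An attrition rate of < 20% at 12-month follow-up is considered indicative of feasibility" (Attrition rate). Losing 8 of 40 is exactly 20%, so at most 7 may be lost, and 40 − 7 = 33.

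**Assumptions, not in the article**
- Typical completion time t, varied from 20 to 50 min.
- A survey can be left open or resumed with its start time unchanged.

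**Break-even elapsed time.** If n − 1 surveys take t minutes and one takes X, the mean is [(n − 1)t + X]/n. It reaches 60 at X = 60n − (n − 1)t.

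| t (min) | n = 40 | n = 33 |
|---|---|---|
| 20 | 2400 − 780 = 1620 min = 27.0 h | 1980 − 640 = 1340 min = 22.3 h |
| 30 | 2400 − 1170 = 1230 min = 20.5 h | 1980 − 960 = 1020 min = 17.0 h |
| 45 | 2400 − 1755 = 645 min = 10.75 h | 1980 − 1440 = 540 min = 9.0 h |
| 50 | 2400 − 1950 = 450 min = 7.5 h | 1980 − 1600 = 380 min = 6.3 h |

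**One survey paused for exactly one day.** The mean becomes t + 1440/n.
- n = 40 adds 36.0 min: 56.0 at t = 20 (pass), 66.0 at t = 30 (fail), 81.0 at t = 45 (fail).
- n = 33 adds 43.6 min: 63.6, 73.6 and 88.6 (all fail).

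**One survey paused for two days.** The mean becomes t + 2880/n. The most favourable case, n = 40 and t = 20, gives 20 + 72 = 92.0 min, so every per-survey case fails.

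**If the four follow-ups were pooled.** The word each in the criterion could mean each survey wave, or baseline on one side and all follow-ups on the other. With n = 4 × 40 = 160, X = 9600 − 159t:
- t = 20: 6420 min = 4.5 days
- t = 30: 4830 min = 3.4 days
- t = 45: 2445 min = 1.7 days

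Baseline, with n about 40, is exposed under either reading.

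**The median in the same scenarios.** It stays at t (20 to 50 min) throughout, so it passes wherever the mean fails.

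**The case against.** The strongest reply is that the mechanism is not documented. Nothing says that the survey can be saved and resumed, or how a re-opened survey is time-stamped. The reminder sentence also covers someone who never opened the survey, who would then start afresh with a normal duration. This stands: interruption with an unchanged start time is an assumption. A page simply left open would have the same effect, however, and the reminders make late finishing plausible.

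Second, the size depends on the typical time, which is also not given. This stands too, and is why a range is shown. The shorter break-even times need a slow typical survey, and the shortest of all also need attrition close to its limit. An interruption of a few hours in one survey does not reach the break-even in any case calculated.

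Third, the distortion would be visible. With 40 respondents, 39 of them at 35 min and one at 1440 min, the mean is (39 × 35 + 1440)/40 = 70.1 min and the SD is (1440 − 35)/√40 ≈ 222 min. The article also undertakes to document difficulties in collecting and analysing the data. That makes an unnoticed error unlikely, but the threshold would still have failed, with no agreed rule for setting the result aside.

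Fourth, handling of interrupted sessions and of phone or in-person completion can fairly be left to a fuller document. Agreed, and the point does not rest on it. The choice of the mean of clock times is stated in the article itself.

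A reader might go further and infer that a few pauses will settle the verdict at every wave, or that a sound survey will be shortened without cause. The documents support neither. Some one-day pauses pass, and the criterion names no consequence of failure, unlike the recruitment criterion (more sites or duration) and the transfer-of-care criterion (a changed triage process).

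**Conclusion.** The point holds as a minor one, with moderate confidence. As written, the criterion counts idle time as completion time and applies its limit to a statistic that one value can move. On the two stated assumptions, a single interruption of roughly a quarter of a day to just over one day is enough to fail it for one survey wave, and a two-day interruption fails it in every per-wave case. Pooling the follow-ups would raise this to days. The consequence is a possible false finding of unacceptable burden, which could mislead planning of the full trial. It is not shown that this will happen, nor that any change to the survey would automatically follow.

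**What to change.** Under Duration of survey completion, apply the 60-minute threshold to the median elapsed time, separately for baseline and for each follow-up survey, and also report the percentage of finished surveys that took more than 60 minutes. Naming each survey also settles whether follow-ups are pooled.

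The cost is one sentence. The start and end times are already to be collected, so no new data are needed. The small downside is that a median responds less to a few respondents who really are slow; the percentage over 60 minutes keeps them in view.

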#### Attrition rate

Retention will be evaluated by rate of attrition. An attrition rate of < 20% at 12-month follow-up is considered indicative of feasibility. Research has suggested that > 20% attrition threatens study validity [60].

### Feasibility of implementing the APP model of care

#### Care provided

Health care provided at the Chronic Pain Clinic will be collected from the electronic medical record (EMR), including prescriptions for medications, interventions delivered, requisitions for diagnostic imaging, referrals to other HCPs, visits to HCPs from each professional background, and relevant notes to employers or insurers. For the feasibility study, the collection of this information will be used to reduce uncertainty around the care provided as part of the APP model of care in the full trial and the capacity of the APP to develop a plan of care and appropriately integrate other team members where needed. The model will be considered feasible if the APP can successfully fulfill the role for at least 80% of participants without having to transfer care to the physician or nurse practitioner as the responsible provider. If more than 20% of participants request transfer of care to the physician or nurse practitioner, or the APP decides a transfer of care to the physician or nurse practitioner is needed, modifications to the initial RPN triage process will be made in preparation for the full trial.

#### Treatment fidelity

Treatment fidelity will be determined using an APP-reported fidelity checklist (Additional file 3). This will allow us to evaluate consistency of the intervention with the proposed initial assessment and care plan methods. An acceptable level of fidelity will be considered with completion of 100% of screening for pathological concerns (for participant safety) and > 80% for all other assessment items.

### Assessment of contextual factors that may influence implementation

Contextual factors that may influence implementation will be evaluated using semi-structured interviews with patient participants and HCPs using an interpretive description approach [61]. Contextual factors that will be explored will include patient participant (e.g., acceptability, satisfaction with the model of care), provider (e.g., trust, perceived value), and clinic level (e.g., perceived influence on clinic processes) barriers and facilitators. We anticipate that the findings from these qualitative interviews will lead to strategies for refining the model of care and associated processes prior to a fully powered trial. We will recruit 10–12 patient participants using purposive sampling with the aim of ensuring maximum variation in age, sex, gender, and duration and location of pain. We will recruit 5–10 HCPs using a convenience sample of health professionals within the Chronic Pain Clinic team. We will aim to include at least one member of each health professional group represented within the team (i.e., medicine, nursing, nurse practitioner, occupational therapy, psychology, physiotherapy, and social work). The interviews will be conducted by a member of the research team over Zoom or through phone call and will last approximately 30 to 60 min. An interview guide will be developed by the interdisciplinary research team and informed by previous studies aimed to explore contextual factors related to the implementation of new advanced practice roles [42, 62]. The qualitative interviews will be recorded and transcribed verbatim. To ensure confidentiality, the data from the interviews will be de-identified before analysis. Data analysis will be conducted using NVivo data management software through a reflexive thematic analysis approach [63]. To ensure rigor, two independent researchers will code the data and conduct the analysis iteratively to ensure reliability of the coding and reduce researcher bias. Researchers will practice reflexivity by maintaining a reflexivity journal and participating in frequent reflexive dialogue among research team members. The researchers will keep an audit trail of the coding process and how themes were generated to ensure transparency.

Patient participant interviews will be completed approximately 1–2 months after their initial visit with the APP, and HCP interviews will occur 1–2 months after the last patient participant has been assessed by the APP. This recall period was considered appropriate given the complexity and context of the questions to be asked for this element of the study [64]. Waiting for all participants to be assessed allows HCPs the full opportunity to be exposed to the APP model of care. The interviewer will ask participants to identify barriers and facilitators to the implementation of the APP model of care and strategies for refining the model of care for the full trial. HCP participants will be asked about the impact on clinical processes and patient care.

Descriptive details regarding the interviewed patient participants will include age, sex, gender, living status, annual household income, education, location of pain, duration of pain, and primary diagnosis causing chronic pain. For the HCPs interviewed, descriptions of their health profession, number of years practicing, and number of years working at the KHSC Chronic Pain Clinic will be described.

### Assessment of outcomes in preparation for the full trial

As part of assessing the feasibility of collecting all assessment data, we will collect all patient participant health outcomes, care provided, flow through the Chronic Pain Clinic, and data for the planned cost utility analysis to inform our intended methods for a fully powered clinical trial. Unless indicated otherwise, these outcomes will be collected using Qualtrics and will be collected at all time points (baseline, 3, 6, 9, and 12 months).

### Participant health outcomes

*Pain severity* and *pain interference* will be captured using the Brief Pain Inventory (BPI) pain severity subscale and pain interference subscale. Both subscales use a numeric rating scale from 0 to 10, with higher scores indicating greater pain or interference, respectively. The BPI shows good reliability and validity for its use among individuals with chronic pain [65] and is the planned primary patient participant health outcome for a full trial.

*Health-related quality of life* will be examined using the EuroQOL-5D-5L [66]. This measure will be used in a cost-utility analysis with the aid of corresponding calculated quality-adjusted life years (QALYs) [67–69]. A value set derived for the Canadian context will be applied to this outcome measure [70].

*Psychosocial risk factors for pain* that are prognostic indicators for outcomes of chronic pain management will be evaluated using the Pain Catastrophizing Scale [71, 72], Tampa Scale of Kinesiophobia [73], and Pain Self-Efficacy Questionnaire [74].

*Self-reported rating of change* will be measured, at follow-up time points, using a global rating of change scale (GROC). The GROC will use an 11-point scale (− 5 to + 5), with negative values representing a perceived worsening and positive values a perceived improvement in functional abilities. The GROC is recommended as a valid self-reported measure of change [75, 76].

*Satisfaction with care* will be assessed using an 11-point scale (0 to 10) at all follow-up time points [77, 78]. Low scores demonstrate dissatisfaction, and positive score suggests satisfaction with care.

*Adverse events* will be monitored and reported using an adverse events questionnaire that is in accordance with event reporting guidelines [51, 79]. This section of the survey requests information regarding the type of adverse event experienced, how long the event lasted, how bothersome the event was (0–10 scale), and what the participant thought caused the event.

### Flow of participants through the Chronic Pain Clinic

One of the goals of the APP model of care is to improve patient flow through interprofessional chronic pain clinics. We hypothesize that the APP model of care may improve patient flow by triaging appropriate participants to care from interprofessional team members other than the physicians (anesthesiologists or other pain specialists) and nurse practitioners directly to those services. There are many services within chronic pain clinics that have much shorter wait-lists (e.g., interprofessional self-management programs, physiotherapy, occupational therapy, social work). Triaging participants appropriate to these services earlier would improve the flow of patients to those services and potentially improve the flow for those who require the specialized services of the anaesthesiologists or nurse practitioners (e.g., medication management or procedures such as injections) by off-loading some of the initial assessment responsibilities from these team members; therefore, we will assess the proportion of participants who are triaged to health services without individual appointments with physicians or nurse practitioners as a feasibility measure for the potential for this model of care to impact patient flow in a future trial.

### Cost-utility analysis

A cost-utility analysis of the APP model of care compared to the physician-led model is planned for the full trial using a societal perspective [80, 81]. Healthcare utilization measures will be captured in the survey and used to determine costs. These utilization measures will include emergency department visits, overnight hospitalizations, diagnostic imaging, surgical interventions, pain injections/procedures, primary care visits (including walk-in clinic visits), specialist physician visits, medications used, physiotherapy, occupational therapy, chiropractic appointments, self-care assistance, and other health provider visits (e.g., massage therapy, social worker visits, psychologist appointments). The survey will capture these measures using specific, pointed questions; for example, “Over the past 12 weeks, how many times did you visit the emergency room for your chronic pain?”.

Direct healthcare costs will be calculated using the Ontario Ministry of Health and Long-Term Care Schedule of Benefits for publicly funded health services and the Ontario Drug Benefit formulary for medication costs. For private healthcare services (e.g., PT in the community), the mean cost for the services in Kingston, Ontario, will be used.

Indirect or non-healthcare costs will be restricted to loss of productivity using a human capital approach. A dollar value will be assigned to time lost from paid employment (part-time, full-time, and self-employment) based on the mean wage in Ontario, according to Statistics Canada. The minimum wage in Ontario will be used to assign a value to time lost from volunteering, caregiving, or homemaking activities. Participants will also be able to report, in the survey, any other out-of-pocket expenses they may have incurred as a result of their chronic pain.

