**Methods:**

This will be a single-arm feasibility study with embedded qualitative interviews to assess contextual factors influencing implementation by exploring participant and provider perspectives. Approximately 40 adults with chronic musculoskeletal pain referred for care at an interprofessional chronic pain clinic will be invited to participate in the feasibility study. Approximately 10–12 patient participants and 5–10 health professionals from the interprofessional team will be interviewed using an interpretive description approach. The APP model of care will involve participants seeing a physiotherapist as the first point of contact within the interprofessional team. The APP will complete an initial assessment and make care recommendations. Outcome measures planned for the full trial will be reported descriptively, including pain severity, pain interference, health-related quality of life, psychosocial risk factors for chronic pain, treatment satisfaction, perceived change, healthcare utilization, and healthcare costs over one year.

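### The printed utilization question looks back 12 weeks but surveys are 3 months apart, so any item with that window misses about 4 of 52 weeks and understates one-year use by about 8% unless rescaled

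*Protocol article*

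**What the plan says.** The Cost-utility analysis section takes healthcare use for costing from the survey. It introduces the question wording with "The survey will capture these measures using specific, pointed questions; for example" and prints one item: "Over the past 12 weeks, how many times did you visit the emergency room for your chronic pain". No other item's recall window is shown.

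The Evaluation and outcome measures section schedules follow-up "at 3, 6, 9, and 12 months after the initial assessment". The section on outcomes in preparation for the full trial says that, unless indicated otherwise, these data "will be collected at all time points (baseline, 3, 6, 9, and 12 months" (closing bracket omitted).

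Under Analysis, each cost is a count multiplied by a unit cost, and these are added up. "The mean cost for the entire study period, as well as the mean cost for each time interval, will be presented". The abstract describes the target as "healthcare utilization, and healthcare costs over one year". No adjustment from 12 weeks to the length of the survey interval is mentioned.

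**The concern.** Three months is about 13 weeks, so a 12-week look-back leaves about one week of each interval that no question covers. Adding the four follow-up counts gives 48 weeks of use under a label of one year.

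Two things are at stake. First, the descriptive one-year cost from this study would be too low for every item with this window. Second, these data are collected to prepare the full trial's cost-utility analysis. If the instrument carries over unchanged, about 48 weeks of cost would be set against 12 months of QALYs.

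The gap also falls in a fixed place. On schedule it is the first week of each interval, and the first such week directly follows the initial APP assessment, when care arising from the new plan may begin. Early care is also where an APP-first and a physician-first model might differ in the full trial.

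**Working it through.** The protocol states no coverage figure, so there is none to reproduce.

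**Inputs**
- Recall window: 12 weeks = 84 days (Cost-utility analysis, the printed item).
- Follow-up surveys: 4, at months 3, 6, 9 and 12 (Evaluation and outcome measures).
- Target period: one year (abstract, Methods). Its length is a calendar fact: 364 days (52 weeks), 365 or 365.25.
- Day 0 is taken as the initial APP assessment, because the Intervention section has the APP perform the initial intake assessment.

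**Step 1. Days asked about.** 4 × 84 = 336 days = 48 weeks.

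**Step 2. Shortfall = 1 − 336 / year length**

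| Year length (days) | Days not asked about | Shortfall | Per interval (days) |
|---|---|---|---|
| 364 | 28 | 7.7% | 7.0 |
| 365 | 29 | 7.95% | 7.25 |
| 365.25 | 29.25 | 8.0% | 7.3 |

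**Step 3. Where the gap falls** (surveys on schedule, 365.25/4 = 91.3 days apart)

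| Survey | Day | Window asked about | Not asked about |
|---|---|---|---|
| Month 3 | 91.3 | 7.3 to 91.3 | 0 to 7.3 |
| Month 6 | 182.6 | 98.6 to 182.6 | 91.3 to 98.6 |
| Month 9 | 273.9 | 189.9 to 273.9 | 182.6 to 189.9 |
| Month 12 | 365.25 | 281.25 to 365.25 | 273.9 to 281.25 |

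The baseline survey cannot fill the first gap, because it is completed before the visit and looks further back.

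**Step 4. Effect on total cost.** If a share *s* of cost comes from 12-week items and use is even over time, the shortfall in total cost is *s* × 8.0%.

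| Share *s* (assumed) | Total cost short by |
|---|---|
| 25% | 2.0% |
| 50% | 4.0% |
| 75% | 6.0% |
| 100% | 8.0% |

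**Step 5. Correction factor.** 91.3/84 = 1.087. Check: 336 × 1.087 = 365.2 days.

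**The case against.** The strongest reply is that one example is not the instrument. The wording is given as an illustration. The windows for admissions, imaging, medications, out-of-pocket spending and lost work time are not printed, and a journal article may leave rescaling to a costing plan. This stands as a limit: a reader might infer that every count and the whole one-year cost are 8% low by construction, and the document does not support that. It supports 8% for items worded like the example, and 2% to 8% for total cost over the shares shown. Respondents may also read 12 weeks loosely as three months, which would reduce the loss.

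It can also be said that little depends on this. The study has one arm, costs are descriptive, no feasibility threshold uses them, and in the full trial the same wording would apply to both arms. That limits the severity. However, a common shortfall would still shrink an absolute cost difference by about 8% under the same assumptions, and it would not be common if early care differs between the arms. The Discussion allows survey questions to be changed if unexpected answers reveal ambiguity. These counts would look plausible, so that check is unlikely to detect the problem.

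The medical record is not limited to 12 weeks, but the Care provided section uses it for care at the clinic, while the cost section names the survey as its source.

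Two further inferences are tempting, and neither holds:
- *The weeks between the baseline survey and the APP visit are also lost from the year.* The Recruitment and consent section says that participants are "enrolled in the study prior to completing the baseline assessment and scheduling an appointment with the APP". That places enrolment before both steps but does not order the two. Follow-up is timed from the initial assessment, so weeks before the visit lie outside the 12 months being costed.
- *Late completion makes the undercount larger.* Each survey still counts 84 days whenever it is answered, so the four still sum to 336 days of use. Under even use, lateness changes which days are sampled but not the size of the shortfall.

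**Conclusion.** The point holds for items that use the printed window. The 12-week recall, the 3-month schedule and the unscaled sum do not fit together, and about 4 of 52 weeks go unasked. One-year use for such items is understated by 7.7% to 8.0%. This assumes use is even over time, all four surveys are completed, respondents take 12 weeks literally, and no rescaling is applied. If use in the first week of an interval differs from the rest, the true loss could be above or below 8%. The effect on total cost depends on the share from such items, which the document does not give.

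Severity is minor to moderate. No feasibility decision in this study changes. The reason to act is that the instrument is meant for the full trial, where cost and QALYs should cover the same period.

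**What to change.** Change the recall wording at each follow-up to *over the past 3 months*. A tighter alternative is a dated window: at month 3, since the initial assessment on [date]; after that, since the previous scheduled follow-up date. If dated windows are used, state the end date as well (the current scheduled date), so that a survey answered late does not count the same days twice. Anchoring to scheduled dates, and not to the last survey completed, keeps pre-visit use out of the first interval and keeps recall at about three months after a missed survey.

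If the survey is already in the field, multiply each 12-week follow-up count by 91.3/84 = 1.087, state this in the analysis, and report scaled and unscaled results. The one-year total should use the four follow-up surveys only: adding the baseline window would count 60 weeks, and 60/52.18 = 1.15, or 15% over a year.

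The cost is a change of survey wording or one line of analysis code. The downside of rescaling is that it assumes even use within each interval and so cannot recover anything particular to the first week after the visit. The wording change has no such limitation.
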